#### Compliance check

2.6.3

Compliance will be checked by counting the returned pouches. To stimulate compliance, participants will be contacted by telephone and reminded during follow-up visits.

#### Power calculation

2.6.4

To detect changes in LDL-C levels, 27 participants per group will be selected, based on the results of a previous intervention study using red yeast rice, assuming a power of 80% and a 2-sided alpha level of 0.05.^[12,13]^ Assuming a 20% dropout rate, the sample size will be estimated at 34 participants per group.

### Statistical analysis

2.7

Data analysis will be conducted by well-trained statisticians, not associated with the research team. Data will be examined for the presence of normality, outliers, violations, and/or missing data. A per-protocol analysis of the participants, who follow the protocol and complete the study, will be carried out. Baseline characteristics will be compared between groups using the Student *t* test. Continuous normally distributed variables will be compared between groups using analysis of covariance or linear mixed effect model. Pearson χ^2^ test or Fisher exact test will be used for categorical variables. For inter-group analysis, paired *t* test or Wilcoxon signed-rank test, will be performed for continuous variables. A *P*-value <.05 will be considered statistically significant. All analyses will be conducted using the SAS software. If needed, models will be adjusted for relevant confounding variables, and a stratified analysis will be performed.

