### Study design

2.1

This study is a randomized, double-blind, placebo-controlled, parallel group study with 2 intervention arms for investigating the effectiveness and safety of yellow yeast rice in controlling blood cholesterol levels. After obtaining informed consents from all participants and completing a baseline evaluation, including a brief medical examination to determine eligibility, participants who meet the eligibility criteria will start a 2-week run-in period, in which they have to follow the guidelines for diet and lifestyle control. After the 2-week run-in period, participants will be randomized into either the test or placebo group.

Figure 1 shows a schematic depiction of the study design.

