### Randomization, allocation concealment, and blinding

2.4

Randomization sequence is computer generated by an independent statistician. All the labeled test and placebo products are provided by Daesang Co, Ltd (Seoul, South Korea). The randomization numbers are kept in opaque sealed envelopes. Group assignments are not revealed and are blinded to the participants and investigators throughout the entire study. The participants who meet the eligibility criteria are randomly assigned (1:1) to either receiving either placebo or yellow-yeast-rice-treated group. Randomization is stratified by gender. Allocation concealment is maintained since no sealed envelope is opened during the study.

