### Handling of withdrawal

2.5

Participants can withdraw their consents for any reason at any time. If any participant wishes to withdraw, investigators will ask about the reason for the withdrawal. Incidences of participant loss, follow-up and withdrawal, will be recorded and reported.

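### The only analysis population named is per-protocol completers, in a randomised placebo-controlled trial that plans for 20% dropout, so the LDL-C comparison is open to bias of unknown size in either direction

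*Protocol article*

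**What the plan says.** Section 2.1 (Study design) sets out the trial: "This study is a randomized, double-blind, placebo-controlled, parallel group study with 2 intervention arms". Section 2.4 gives 1:1 allocation, stratified by gender.

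Section 2.7 (Statistical analysis) names the population: "A per-protocol analysis of the participants, who follow the protocol and complete the study, will be carried out". No intention-to-treat, full analysis or all-randomised set is mentioned there or elsewhere. The section offers analysis of covariance or a linear mixed effect model for normally distributed continuous variables. It says that missing data will be looked for, but gives no rule for handling them.

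Section 2.6.4 (Power calculation) starts from 27 per group and then states: "Assuming a 20% dropout rate, the sample size will be estimated at 34 participants per group". Section 2.5 (Handling of withdrawal) says of those who leave: "Incidences of participant loss, follow-up and withdrawal, will be recorded and reported". It does not say whether they are analysed. Section 2.6.2.1 has the lipid profile measured at baseline, week 4 and week 8.

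**The concern.** The trial asks whether yellow yeast rice lowers LDL-C compared with placebo. Randomisation protects that comparison only while people are analysed in the groups they were assigned to. Whether someone completes or follows the protocol is settled after assignment and can depend on the product, for instance through tolerability. If the reasons for leaving differ between the arms and are related to LDL-C, the completer groups differ for reasons other than the product.

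The sample size points the same way: it is inflated so that 27 of 34 per group remain, which treats dropouts as lost to the analysis. A main result on that basis could not be read as the effect of being assigned the product. A false difference could appear, or a real one could be hidden.

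**Working it through.** **1. The plan's own figure.** Inputs from section 2.6.4: 27 evaluable per group, 20% dropout. 27 / (1 - 0.20) = 33.75, rounded up to 34 per group, 68 in total. This reproduces, and the sample-size arithmetic is not at fault.

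**2. How many are left out.** 0.20 × 68 = 13.6, about 14 participants. More would be left out if completers who did not follow the protocol are also removed.

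**3. Possible bias.** The article gives neither an SD nor any pattern of dropout, so these inputs are assumptions: SD 25 mg/dL, no true effect, 34 per arm with 7 leaving each arm, and correlation r between leaving and a poor LDL-C outcome.

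Closed form for one arm: if the worst 20% on a standard normal score leave, the mean of the rest shifts by φ(0.842)/0.80 = 0.280/0.80 = 0.35 SD. With correlation r the shift is 0.35 × r × 25 = 8.75 × r mg/dL, that is 2.6, 4.4 and 6.1 mg/dL at r = 0.3, 0.5 and 0.7. Simulation agrees:

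| Where dropout depends on outcome | r = 0.3 | r = 0.5 | r = 0.7 |
|---|---|---|---|
| Active arm only | -2.6 | -4.3 | -6.2 |
| Placebo arm only | +2.6 | +4.4 | +6.0 |
| Both arms alike | about 0 | about 0 | about 0 |

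(Bias in mg/dL, active minus placebo; a negative value favours the product.)

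With the active arm only, the nominal 5% test rejects in about 7%, 10% and 16% of trials. With both arms alike it rejects in 5.2%, 5.8% and 6.9%. If leaving is unrelated to outcome there is no bias.

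**4. Scale.** Section 2.6.4 gives 80% power and two-sided alpha 0.05 but no effect size. Back-solving at 27 per group gives (1.960 + 0.842) × √(2/27) = 0.76 SD by the normal formula, or 0.78 SD by the t test. At the assumed SD that is 0.78 × 25 = 19.5 mg/dL. The illustrated bias is therefore 2.6/19.5 = 13% to 6.2/19.5 = 32% of the effect the trial is sized for.

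**5. What an all-randomised analysis does to power.** Taking 0.78 SD, 34 measured per group and an assumed dilution:

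| Effect kept | Power at 34 per group | Evaluable per group for 80% power |
|---|---|---|
| 100% | 88% | 27 |
| 90% | 81% | 27/0.9² = 33.3, so 34 |
| 80% (the 20% who leave get no benefit) | 71% | 27/0.8² = 42.2, so 43 |

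**6. When the mixed model helps.** In a check where active-arm dropout is driven by the week-4 value (week-4 to week-8 correlation 0.7, assumed), the completer estimate is off by -6.1 mg/dL. Using the dropouts' week-4 data brings that to about 0. In step 3 dropout is tied to the final, unobserved outcome; a mixed model would not generally remove that bias.

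**The case against.** The strongest reply is that section 2.7 says a per-protocol analysis will be done. It does not say that it is the only or the primary one. The text is a condensed article, a statistical analysis plan may exist, and the CONSORT diagram is not shown. It stands that an all-randomised analysis is not expressly ruled out. But the article did choose a population and name it, it names no other, and the power calculation fits that choice. This is more than a detail left for later.

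A reader might infer that the bias favours the product. The documents do not support this. Nothing in them suggests that leaving depends on outcome in the active arm only. Leaving because of no apparent benefit would act at least as plausibly on placebo, which pushes the other way. Participants are blinded, and the article does not say that they learn their lipid results during the trial.

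A reader might also infer that the plan throws away the week-4 values of people who leave later. That follows only if the completer restriction governs every analysis, and the article does not say so.

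It also stands that the amount of recoverable data is unknown. Anyone who leaves before week 4 has no post-baseline LDL-C, and section 2.5 allows consent to be withdrawn at any time.

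**Conclusion.** The point holds in this form: per-protocol completers are the only population named, at a planned dropout of about 14 of 68, and the comparison is therefore open to bias whose size and direction cannot be known from the document. The range of about -6 to +6 mg/dL is an illustration. It rests on an assumed SD of 25 mg/dL, no true effect, correlations up to 0.7 and outcome-related dropout in one arm only; it vanishes when both arms share the mechanism. That this is a superiority question is inferred from the placebo control, the two-sided test and the effectiveness aim, since the article does not use the word. The choice of population decides what the main result means, so it should be corrected before analysis.

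**What to change.** - State that the primary analysis includes all randomised participants in their assigned groups, regardless of adherence.
- Use the linear mixed model already named, with baseline, week-4 and week-8 LDL-C and adjustment for sex, the stratification factor, so that week-4 values of later dropouts contribute.
- Ask participants who stop the product, but do not withdraw consent, to attend the remaining blood draws. This also limits reliance on the model's assumption about why data are missing.
- Keep the per-protocol analysis as supportive, with membership fixed before unblinding.

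The cost in text is one paragraph on analysis and one sentence on visits. The statistical cost is possible dilution. The plan should state that power with 34 measured per group runs from about 88% (undiluted) through 81% (10% dilution) to 71% (20% dilution), and that in the last case 43 evaluable per group would be needed for 80%. Whether more participants are needed depends on the dilution the sponsor considers realistic.

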### Study population and eligibility criteria

2.2

The study population is adults aged 20 to 45 years old. Assuming a 20% dropout rate, 68 eligible participants will be recruited from a single center, Seoul Metropolitan Government-Seoul National University Boramae Medical Centre.

Eligible participants are those who meet all the following inclusion criteria and none of the listed exclusion criteria.

*Inclusion criteria*:1.Voluntary agreement to participate and sign the written informed consent forms2.Men and women (aged 20–45 years, premenopause)3.Body mass index (BMI) = 18 to 30 kg/m^2^4.Fasting LDL-C levels: ≥130 mg/dL5.Fasting triglyceride levels: <300 mg/dL

*Exclusion criteria*:1.Continuous use of drugs that affect lipid metabolism or inflammation within 4 weeks before the first visit2.Continuous ingestion of health functional foods (plant sterols, omega-3 fatty acids, aloe, chitosan, onion extract, etc) and oriental herbal medicines that affect lipid metabolism and inflammation within 4 weeks before the first visit3.Weight loss therapy or weight change of more than 10% within 6 months before the first visit4.Having any of the following diseases:Myocardial infarction, stroke, or hypertensionDiagnosed diabetes or fasting blood glucose level >126 mg/dL at the first visitLiver dysfunctionRenal impairmentChronic inflammatory bowel diseaseAutoimmune diseases, hyperthyroidism, hypothyroidism, or malignant tumors5.Women receiving hormonal therapy6.Excessive smokers (≥1 pack/d)7.Alcoholics or consuming >140 g/wk8.Regular intensive exercise (>10 h/wk)9.Participation in other clinical studies within 4 weeks before the first visit10.Allergy to yellow yeast rice11.Pregnant or lactating women

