##### Effective variables

2.6.2.1

At baseline, 4, and 8 weeks after intervention, lipid profile, lipoproteins, glucose levels, and inflammation markers will be analyzed. Gene expression of markers related to cholesterol metabolism in PBMCs, such as 5-hydroxy-3-methylglutaryl-coenzyme A and LDL receptor, will be also analyzed using quantitative real-time polymerase chain reaction.

Brachial-ankle pulse wave velocity will be measured at baseline and 8 weeks after intervention. The measurements will be performed after the participant's rest for 15 minutes in the supine position.

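### Section 2.7 admits a continuous outcome to ANCOVA or the mixed model only if the raw variable is normal, which those models do not require; skewed markers lose most, LDL-C little

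*Protocol article*

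**What the plan says.** All of the following is in the protocol article.

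- **Check.** Section 2.7 (Statistical analysis) begins with a data check: "Data will be examined for the presence of normality, outliers, violations, and/or missing data".
- **Between-arm model.** The same section then says: "Continuous normally distributed variables will be compared between groups using analysis of covariance or linear mixed effect model". Normality is attached to the variable, and LDL-C is not exempted.
- **Other methods for continuous outcomes.** The only others named are the paired t test and its rank counterpart: "Wilcoxon signed-rank test, will be performed for continuous variables". The section labels these as inter-group analyses, but both are paired tests.
- **Covariates.** The baseline value is not named. Adjustment is optional: "If needed, models will be adjusted for relevant confounding variables".
- **Outcomes affected.** Section 2.6.2.1 (Effective variables): "At baseline, 4, and 8 weeks after intervention, lipid profile, lipoproteins, glucose levels, and inflammation markers will be analyzed".
- **Entry limit.** Section 2.2: "Fasting LDL-C levels: ≥130 mg/dL".
- **Sizing.** Section 2.6.4 (Power calculation): "To detect changes in LDL-C levels, 27 participants per group will be selected". No difference or SD is given.

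**The concern.** ANCOVA and linear mixed models make an assumption about the errors, given arm and covariates. They make none about the overall shape of the outcome. In this trial that shape is partly a product of the design: the LDL-C entry limit cuts off the lower tail at screening, and a treatment effect mixes two arms with different means. A check on the raw variable can therefore fail while the model fits well.

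Two things are at stake. An outcome that fails is sent away from the adjusted model and loses precision, and on the text as written it has no between-arm comparison at all. And the test used for LDL-C, on which the trial is sized, would depend on the outcome data instead of being fixed beforehand.

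The mislabelled paired tests are a separate fault. Replacing them with a correct two-sample rank test would leave the entry condition in place.

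**Working it through.** **1. The plan's own figure.** 27 evaluable per arm with 20% dropout: 27 / (1 − 0.20) = 33.75, rounded up to 34. This agrees with section 2.6.4. The 27 itself cannot be rebuilt, because no difference or SD is stated. Solving backwards at 80% power and two-sided 5%: d = (1.960 + 0.842) × √(2/27) = 0.762, or 0.777 with the t distribution.

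**2. Assumed inputs (none is in the protocol).**
- Check: Shapiro-Wilk at 5%, both arms pooled, 27 per arm.
- LDL-C: usual mean 110-125 mg/dL, between-person SD 25-30, within-person SD 10-14, screening value at least 130, effect 0.777 SD of change.
- Skewed markers: log-normal, log SD 0.4-0.9, baseline correlation 0.5-0.7, effect 0.5 log SD.
- ANCOVA includes the baseline value.

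**3. LDL-C: how often the check fails.** Week-8 values fail in about 6-15% of simulated trials, and up to 20% in some settings. Change fails in 4.3-4.8% and ANCOVA residuals in about 4-6%, which is close to the nominal 5%. The stable between-person part, which carries the truncation, cancels in change.

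**4. LDL-C: power.** ANCOVA has 83-84%, and up to 88% in a second set of runs. If the rank test were used in every trial, power would be 54-68% on week-8 values (down to 46% in the second set) and about 77-79% on change. The rule uses the rank test only when the check fails, so roughly:

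loss ≈ failure rate × (ANCOVA power − rank-test power)

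- Week-8 values, mild end: 0.06 × (83 − 68) = 0.9 points.
- Week-8 values, unfavourable end: 0.20 × (88 − 46) = 8.4 points.
- Change: 0.048 × (84 − 77) = 0.3 points.

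Simulating the whole procedure (check, then the test it selects) agrees. The loss is 0.1-0.6 points when change is checked and about 2-8 points when week-8 values are checked. In one set of five settings, four lost about 1-3 points and the least favourable lost 7.6.

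**5. Skewed markers.** The raw check fails in about 85-100% of trials, so the fallback is nearly always used.

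| Procedure | Power |
|---|---|
| Log-scale ANCOVA with baseline | about 54-70% |
| Check, then unadjusted week-8 rank test if it fails | about 40-42% |

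**6. Is the gain from the log scale or from the adjustment?** A separate run used slightly larger effects (0.25 / 0.45 = 0.5 / 0.9 = 0.56 log SD):

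| Log SD | Log-scale ANCOVA | Raw-scale ANCOVA | Rank test, week 8 |
|---|---|---|---|
| 0.45 | 69.2% | 63.4% | 48.7% |
| 0.9 | 69.4% | 49.6% | 49.1% |

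Under strong skew, raw-scale ANCOVA does no better than the rank test. The log scale is then essential.

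**7. Does the check protect the type I error?** With no effect, ANCOVA rejected in about 4-5% of trials in every scenario of that run, LDL-C and skewed markers alike. There was no inflation for the check to prevent.

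**The case against.** The strongest reply is that the sentence is ordinary article shorthand. It names no normality test, no threshold and no object (raw value, change, pooled or per arm), and the violations to be examined may include residual checks. A log-transformed triglyceride could count as a normally distributed variable and enter the model, and a condensed article commonly leaves transformations and covariate lists to the full plan. Some of this stands. The silence on transformation is not itself a fault, and the skewed-marker figures apply only if the raw variable is what is checked. But the article does state a rule, and read plainly the rule tests the variable. If residuals were meant, saying so takes one phrase.

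It is also fair that the baseline covariate is inferred from the term analysis of covariance and is not stated.

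A reader might infer that LDL-C power falls from about 83% to between 54% and 68%. The documents do not support that. Those are powers if every trial used a week-8 rank test, whereas the check would divert only a minority of trials, and the sample-size section speaks of changes in LDL-C, where the loss is under 1 point. A reader might also infer that deleting two words is enough. For strongly skewed markers it is not, as step 6 shows.

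**Conclusion.** The point holds as a badly fixed rule with a cheap remedy. The entry condition tests something the models do not assume, and it leaves variables that fail without a valid between-arm method.

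- **Skewed secondary markers** bear the main cost: about 54-70% power with log-scale ANCOVA against about 40-42% under the rule with an unadjusted rank fallback. Much of that gain can come from the log scale.
- **LDL-C** loses little on average: under 1 point if change is checked, about 2-8 points if week-8 values are checked with an unadjusted week-8 rank test as fallback. The further cost is that its test is picked after seeing the outcome data.

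The direction follows from the text. The sizes do not: they depend on assumed SDs, correlations, normality test and fallback, none of which the protocol gives. An analysis plan that is not shown may settle some of them.

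**What to change.** In section 2.7, remove normality of the variable as the condition for entering the between-arm model, and state that:

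- LDL-C and all other continuous outcomes are compared between arms with the same model, with the baseline value as covariate, whatever a normality check of the raw variable shows;
- triglycerides and inflammation markers are analysed on the log scale, fixed before unblinding;
- residuals are inspected, and a rank-based ANCOVA is the sensitivity analysis.

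The cost is wording only, with no extra data or participants. The one downside is that log-scale results must be reported as ratios of geometric means, which some readers find less direct than differences in the original units.

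### The inter-group sentence names paired tests, which cannot compare two unmatched arms; non-normal outcomes are left with only a paired test named

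*Protocol article*

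**What the plan says.** Section 2.1 describes a "randomized, double-blind, placebo-controlled, parallel group study with 2 intervention arms". Section 2.4 has participants "randomly assigned (1:1) to either receiving either placebo or yellow-yeast-rice-treated group", and the only restriction on the randomization is this: "Randomization is stratified by gender". Nothing matches individuals across arms.

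Section 2.7 then gives these rules for continuous data:

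- A check of distributions: "Data will be examined for the presence of normality, outliers, violations, and/or missing data".
- For baseline: "Baseline characteristics will be compared between groups using the Student *t* test".
- For outcomes: "Continuous normally distributed variables will be compared between groups using analysis of covariance or linear mixed effect model".
- Two sentences after that: "For inter-group analysis, paired *t* test or Wilcoxon signed-rank test, will be performed for continuous variables".

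The same section assigns chi-square or Fisher tests to categorical variables, and allows confounder adjustment and stratified analysis if needed. It names no rank-sum test, transformation or other independent-samples method for a continuous outcome that fails the normality check.

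**The concern.** A paired t test or a signed-rank test works on differences within pairs. Here the only natural pairs are a participant's own values at two visits. Between the arms there are none, so the sentence as written assigns tests that do not fit the comparison. Applied literally, the result would depend on an arbitrary ordering of participants, and it could not use everyone if the arms finished with different numbers.

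If the word is corrected to intra-group, the tests become before-after tests within each arm. They are legitimate as description but do not estimate or test the treatment effect. The between-arm rule that remains covers normally distributed variables only. The outcomes in section 2.6.2.1 include lipids, inflammation markers and gene expression. Some of these may well be skewed, although the article does not say so. For any that are, the text points the analyst only to the signed-rank test. What is at stake is a report that an outcome changed significantly in the active arm but not on placebo, offered in place of a comparison of the arms.

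**Working it through.** **The plan's own figure.** Section 2.6.4 gives 27 evaluable per group and 20% dropout. 27 / (1 − 0.20) = 33.75, rounded up to 34 per group, and 2 × 34 = 68. This reproduces the stated total. The step that leads to 27 cannot be checked because no effect size or SD is given, but the choice of test discussed here does not depend on it.

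**Methods named for continuous variables, side by side (section 2.7).**

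| Situation | Method named | Valid for two independent arms? |
|---|---|---|
| Baseline characteristics | Student t test | Yes |
| Outcome, normally distributed | ANCOVA or mixed model | Yes |
| Outcome, not normally distributed | Signed-rank test only | No, it is a paired test |
| Inter-group, any continuous variable | Paired t or signed-rank test | No |

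Changing inter to intra repairs the last row. The third row still has no between-arm method.

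**Literal reading.** This was simulated with an assumed lognormal outcome (log-SD 0.8), 27 per arm, 10,000 runs and participants paired arbitrarily across arms. With no effect, the signed-rank and rank-sum tests both reject in 4.7% of runs. With a shift of 0.775 SD, power is 92.6% for the signed-rank test and 98.6% for the rank-sum test. The false-positive rate holds, and the cost is some power plus a result that depends on an arbitrary ordering.

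**Within-arm reading.** Assumptions, none of them from the documents: the paired test is run in each arm, the two results are read as the group comparison, there is no treatment effect, and both arms share the same true change of m standard deviations of change. With n = 27 per arm, each test has 26 degrees of freedom and noncentrality m√27. Let p be the chance that one arm reaches two-sided P < .05. The active arm alone is significant with probability p(1 − p), and exactly one arm with probability 2p(1 − p).

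| m (SD) | p | Active arm alone | Exactly one arm |
|---|---|---|---|
| 0 | 0.050 | 0.050 × 0.950 = 4.8% | 9.5% |
| 0.1 | 0.079 | 7.3% | 14.6% |
| 0.2 | 0.170 | 14.1% | 28.3% |
| 0.3 | 0.324 | 21.9% | 43.8% |
| 0.4 | 0.517 | 25.0% | 49.9% |
| 0.5 | 0.706 | 20.8% | 41.5% |
| 0.7 | 0.938 | 5.8% | 11.6% |

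Since p(1 − p) cannot exceed 0.25, the row near 0.4 SD is the worst case and not a typical one. Simulation of the same set-up gave 4.7%, 21.9%, 25.3% and 20.8% for the active arm alone at 0, 0.3, 0.4 and 0.5 SD, in agreement.

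**The case against.** The strongest reply is that this is a one-word slip. A between-group model is named two sentences earlier, and the paired t and signed-rank tests are the usual pair for before-after change. Read together, the section describes between-group models plus within-group tests. That reading is very likely right, and it stands. It does not dispose of the point, because the model is restricted to normally distributed variables and the only non-parametric test named is still a paired one.

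A second reply is that the handling of non-normal outcomes belongs in the full protocol or SAP, which are not shown. In part this stands: the missing rank-sum test or transformation would be no finding by itself, and a log-transformed variable that became normal would fall under the existing ANCOVA sentence. But the article is not silent. It addresses the inter-group analysis and names tests that do not fit, so a correct SAP would contradict it.

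Three stronger readings are tempting and not supported:

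- *That the LDL-C comparison is invalid.* If LDL-C passes the normality check, ANCOVA or the mixed model applies to it.
- *That selection on high LDL-C makes both arms fall by regression to the mean.* This needs the qualifying value to serve as the baseline. Section 2.1 puts a 2-week run-in between the eligibility evaluation and randomization, section 2.6.2 lists first screening and baseline separately, and section 2.6.2.1 measures lipids at baseline. A fresh baseline would absorb the selection effect. Section 2.1 also uses the word baseline for the eligibility evaluation, and Table 1 is not shown, so the timing is uncertain; the argument cannot be relied on.
- *That about half of null trials would show one significant arm.* That is the ceiling of 2p(1 − p), reached only near 0.4 SD, and nothing in the article says that within-arm results will replace the planned model.

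**Conclusion.** The point holds in limited form. The sentence is wrong as written for two unmatched arms, probably through a slip of one word. Normally distributed outcomes already have a valid between-arm method; for non-normal continuous outcomes the article names only a paired test. That some outcomes will be non-normal is an assumption.

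The harm is conditional. If within-arm tests were read as the group comparison, a null trial would show significance in the active arm alone somewhere between about 5% and 25% of the time, depending on a shared change that the documents do not give. If the sentence were followed literally, the loss would be mainly power and reproducibility. The sample size of 34 per group, 68 in total, is unaffected.

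**What to change.** Replace the inter-group sentence with two:

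1. Paired t or Wilcoxon signed-rank tests describe change within each group only, and no efficacy conclusion rests on them.
2. Every continuous outcome is compared between arms by the baseline-adjusted model; where normality fails, the outcome is log-transformed, or compared by an independent-samples rank method (rank ANCOVA, or the Wilcoxon rank-sum test on change).

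The cost is two sentences, with the SAP, if one exists, checked for agreement. No sample size, visit or procedure changes. The article says recruitment is under way, so the wording should be settled before unblinding.
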